#### Secondary outcome

**Parenting stress index – IV – short form (PSI).** Developed by Abidin [35, 36], this 36-item questionnaire includes three subscales: Parental Distress (PD; e.g., “I feel trapped by my responsibilities as a parent”), Parent-Child Dysfunctional Interaction (P-CDI; e.g., “I often have the feeling that my child is misbehaving on purpose”), and Difficult Child (DC; e.g., “My child rarely does things that make me happy”).Touchèque et al. [37] reported alpha coefficients of 0.79 for each of the three subscales (PD, P-CDI, and DC) in a French sample. The 12 items of the P-CDI subscale will be used in this study to assess foster carers’ perceptions of their relationship with the child in their care, using a 5-point Likert scale (1 = Strongly Disagree, 2 = Disagree, 3 = Not Sure, 4 = Agree, 5 = Strongly Agree).

**Marschak interaction method (MIM).** This structured assessment tool is based on attachment and mentalization theories and involves a series of age-appropriate tasks completed by the foster carer and child together [38, 39]. The MIM assesses four dimensions of interaction: Structure, Engagement, Nurture, and Challenge. Interaction recordings will be coded using the Dyadic Emotional Interaction Style (D-EIS), developed in Finland [40] and used internationally. The D-EIS consists of nine items, reflecting the four MIM dimensions, rated on a continuum from 0 (indicating significant difficulties requiring clinical intervention) to 5 (reflecting a very positive relationship not requiring intervention). This coding system yields a total score ranging from 0 to 40, integrating observations of both the child and the caregiver [41]. The MIM manual has been translated into French by certified coders from our research team, with permission from the original developer. In this study, a subgroup of dyads will be assessed using the MIM and D-EIS coding system, with all coding conducted using a double-blind procedure.

**Subjective Measure of Relational Closeness (SMRC).** This measure, developed specifically for this study, includes two items that will be administered to foster carers after completing the MIM: (1) “How emotionally close do you feel to the child currently in your care?” and (2) “How important do you think you are to the child currently in your care?” Each item will be rated on a 5-point Likert scale, ranging from “not at all” to “extremely.”

#### Exploratory outcomes measures

**Parental burnout assessment (PBA).** This 23-item questionnaire assesses parental burnout [42] across four dimensions using a 7-point Likert scale (1 = *Never*, 2 = *Almost never*, 3 = *Sometimes*, 4 = *Regularly*, 5 = *Often*, 6 = *Very often*, 7 = *Always*): (a) exhaustion (e.g., “I feel completely run down by my parenting role”), (b) contrast with previous experience (e.g., “Being a parent is much more difficult than I could have ever imagined”), (c) sense of being overwhelmed in the parenting role (e.g., “I can’t stand my role as a parent anymore”), and (d) emotional distancing from one’s children (e.g., “I have no fun being with my children anymore”). The PBA demonstrates strong internal consistency: α = 0.96 for the total score, 0.93 for exhaustion, 0.90 for contrast and saturation, and 0.79 for emotional distancing [43]. This validation study included a sample of both French-speaking and English-speaking parents (*N* = 901), thus validating the PBA for use with French-speaking populations.

**Service Attachment Questionnaire (SAQ).** This 25-item questionnaire was originally designed to assess attachment security between patients and mental health services [44]. It will be adapted for this study to assess the quality of the relationship between foster carers and their CPS, focusing on five key themes: focusing on five key themes derived from the original six SAQ subscales: (a) feeling listened to (e.g., “I have somebody who listens attentively to me.”), (b) experiencing continuity in the helping relationship (e.g., “I have regular time with the same person that knows me and my problems.”), (c) receiving adequate time and attention (e.g., “I feel under pressure to get better and be discharged.” [reverse-scored]), (d) feeling accepted (e.g., “I feel that people at CPS understand my needs and problems.”), and (e) finding comfort in times of difficulty (e.g., “I have a feeling of being looked after.”). The original SAQ demonstrated good internal consistency (α = 0.93) and test-retest reliability (mean *r* =.74 across subscales) in a sample of 154 service users. This questionnaire has also undergone validation with a sample of *N* = 1181 French foster carers as part of a larger research project on foster care conducted by our research team (validation article in preparation).

**Fidelity of implementation** (**COS-P Fidelity Log).** This log consists of 12 Likert-scale items per session (96 items in total) and reflective questions, allowing facilitators to self-assess the fidelity and quality of program implementation with their group. For the purposes of this study, only the 96 Likert-scale items will be used for data analysis.

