#### Circle of security parenting (COS-P) intervention

The intervention group will participate in the COS-P program in addition to TAU. Foster carers will be assigned to groups of 8 to 10 participants and will attend sessions in dedicated training facilities. The eight 2-hour sessions (detailed in Appendix 3) will be co-facilitated by two child protection professionals certified by Circle of Security International. If a participant misses a session, a 30-minute individual make-up session will be offered before the next group meeting.

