#### Fidelity

To ensure fidelity to the COS-P model, all facilitators will be certified in the program after receiving four days of training. They will complete a fidelity checklist after each session, using the form provided in the intervention manual. Two group supervision sessions will be provided by a trainer accredited by Circle of Security International.

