### Measures

#### Three-time measurement

Following an initial phase (T0), data collection will occur at three time points (see Table 3):

**T1 (Baseline)** Questionnaires, interviews, and interaction assessments will be administered in the week prior to the first COS-P session.

**T2 (3-month f/u)** Questionnaires, interviews, and interaction assessments will be administered three months after the final COS-P session.

**T3 (Qualitative Data Collection at 4-month f/u)** Focus groups will be conducted four months after the completion of the intervention (see Table 4 for an overview of assessments).

**Table 3 Tab3:** SAFE FAMILIES study data collection schedule

	(T0) Enrollment and allocation	(T1) Baseline	COS-*P* group (intervention arm only)	(T2) 3-month f/u	(T3) 4-month f/u
Foster Parent Consent	X				
Biological Parent Consent (video recording)	X				
Sociodemographic and Professional Questionnaire	X				
*Quantitative assessments*					
CCQ		X		X	
PSI		X		X	
PBA		X		X	
SAQ		X		X	
MSPE		X		X	
MIM-DEIS		X		X	
PDI-R		X		X	
COS-P Fidelity Log			X		
*Qualitative assessments*					
Self-Confrontation Interviews		X		X	
Focus-groups					X

**Table 4 Tab4:** Overview of qualitative and quantitative assessments

	Control Group (Gc) + Intervention Group (Gi) *N* = 70	Subgroups of Gi
	Quantitative assessments	Qualitative assessments
**Primary Outcome** Assess foster parent caregiving sensitivity and reflective functioning	CCQ	PDI-R (*N* = 20) Self-confrontation Interviews (*N* = 6)
**Secondary Outcome** Assess the relationship between the foster parent and the child		
	PSI	SMRC (*N* = 20), MIM-DEIS (*N* = 20) Focus Groups

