### Statistical analyses

***Sample size and analysis.*** Sample size calculation was based on an effect size of *d* = 0.38, drawn from a meta-analysis examining the impact of attachment-based interventions on parental sensitivity [49]. An a priori power analysis using G*Power software [50] indicated that 58 participants are needed to achieve 80% power with a significance level of *p* <.05. To account for potential attrition (20%), we aim to recruit 35 participants for each group (intervention and waitlist control receiving TAU).

The data will be analyzed using both quantitative and qualitative methods. Statistical analyses will be conducted using R software. All tests will be two-tailed with a significance level set at *p* <.05.

***Quantitative analyses.*** Descriptive statistics will be used to characterize the sample at baseline (T1) and at each assessment point (T2, T3). This will include frequencies and percentages for categorical variables (e.g., gender) and means and standard deviations for continuous variables (e.g., age, duration of placement). To test the primary hypothesis (H1), a two-way mixed ANOVA will be conducted with Group (Intervention vs. Control) as the between-subjects factor and Time (T1, T2) as the within-subjects factor. The dependent variable will be the CCQ score. To test the secondary hypothesis (H2), a two-way mixed ANOVA will be conducted with Group (Intervention vs. Control) as the between-subjects factor and Time (T1, T2) as the within-subjects factor. The dependent variable will be the PSI score. To explore the potential moderating effects of parental burnout (PBA), perceived emotional support from placement services (SAQ) and fidelity of program implementation, hierarchical multiple linear regressions will be performed. The CCQ and PSI scores at T2 will be the dependent variables, with group allocation (Intervention vs. Control) as the primary predictor. The potential moderators (PBA, SAQ, and fidelity of implementation) will be entered in the model after the main effect of group allocation.

Complementary Analyses for a Subgroup of Foster Carers: A subgroup of 20 foster carers will participate in additional assessments using the Parent Development Interview - Revised (PDI-R) and the Marschak Interaction Method (MIM) coded with the Dyadic Emotional Interaction Style (D-EIS). These assessments will be conducted at T1 (baseline) and T2 (3-month follow-up).

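### Fidelity is rated per COS-P group, giving about four distinct values, yet it enters carer-level regressions whose error rate holds only if carers in the same group are uncorrelated

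*Protocol article*

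**What the plan says.** Four parts of the Protocol article bear on this.

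- **How fidelity is measured.** The Fidelity section says of the facilitators: "They will complete a fidelity checklist after each session". Under Exploratory outcomes measures, the COS-P Fidelity Log has 12 Likert items for each of eight sessions, 96 in all, "allowing facilitators to self-assess the fidelity and quality of program implementation with their group". No fidelity score for an individual carer is described. Table 3 marks the COS-P group column, where the log sits, as "intervention arm only".
- **How groups are formed.** In the COS-P intervention section: "Foster carers will be assigned to groups of 8 to 10 participants". Sessions are "co-facilitated by two child protection professionals".
- **How many carers.** In Statistical analyses: "we aim to recruit 35 participants for each group", with a 20% attrition allowance.
- **How fidelity is analysed.** For burnout (PBA), perceived support (SAQ) "and fidelity of program implementation, hierarchical multiple linear regressions will be performed". The dependent variables are the T2 CCQ and PSI scores, and the moderators follow group allocation in order of entry. *Hierarchical* here therefore means entry in blocks, not a multilevel model. The section mentions no random effect for COS-P group, no clustered standard error and no analysis of group means.

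The list of moderators to be explored, under Study aims and hypotheses, includes fidelity of implementation.

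**The concern.** The predictor varies between COS-P groups and the outcome varies between carers. An ordinary regression on carers treats each carer as a separate piece of evidence about fidelity, although carers in the same group add no new fidelity value. If carers who share sessions, facilitators and peers also resemble one another on CCQ or PSI at T2, the standard error of the fidelity coefficient is too small and chance differences among a few groups reach significance too often.

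This is separate from the absence of fidelity scores in controls. Limiting the analysis to the COS-P arm would solve that problem and leave this one untouched.

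At stake is one exploratory result: a significant fidelity coefficient could be reported as evidence that delivery quality matters when it reflects only which few groups happened to do better.

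**Working it through.** **Plan's own figures.** 12 items × 8 sessions = 96, as stated. The planned size also follows: 58 × 1.20 = 69.6, rounded to 70, or 35 per arm. The protocol gives no figure for the fidelity regression itself, so the rest is derived.

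**Number of distinct fidelity values.** 35/10 = 3.5 and 35/8 = 4.4, so about four groups and about four values. Simple randomization and attrition make 3 to 5 plausible.

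**Degrees of freedom, one predictor, COS-P arm only.**

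| Analysis | Residual df | Critical t (two-sided 5%) |
|---|---|---|
| 35 carers: 35 − 2 | 33 | 2.03 |
| 28 completers (35 × 0.80): 28 − 2 | 26 | 2.06 |
| 4 group means: 4 − 2 | 2 | 4.30 |

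The excess is 33 − 2 = 31 with all carers, or 26 − 2 = 24 with completers. The correlation needed for significance is t/√(t² + df). For carers it is 2.03/√(2.03² + 33) = 0.33. For four group means it is 4.30/√(4.30² + 2) = 0.95.

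**Type I error.** Simulation with no true fidelity effect: a group-level predictor unrelated to outcome, an ordinary carer-level regression, and 8,000 trials per cell. The ICC is assumed.

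| ICC | 35 carers (9, 9, 9, 8) | 28 carers (4 × 7) |
|---|---|---|
| 0 | 4.7% | 5.3% |
| 0.01 | 6.2% | 5.5% |
| 0.05 | 9.6% | 8.8% |
| 0.10 | 14.7% | 13.0% |
| 0.20 | 24.6% | 20.2% |

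A separate run of 20,000 trials gave 5.0%, 10.0%, 14.8% and 23.8% for 35 carers at ICC 0, 0.05, 0.10 and 0.20. Regressing the four group means on 2 df held the error at about 5% throughout.

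**Analytic check.** For a predictor constant within groups the design effect is 1 + (m − 1) × ICC. With m = 35/4 = 8.75 and ICC 0.10 it is 1 + 7.75 × 0.10 = 1.775. The nominal cut-off 2.03 then acts like 2.03/√1.775 = 1.53, whose two-sided tail area on 33 df is about 14%, close to the simulated 15%.

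**Sensitivity, 35 carers.** ICC 0.05, 0.10 and 0.20 in turn:
- three groups (12, 12, 11): 12.1%, 18.1%, 29.2%;
- five groups of 7: 8.7%, 12.2%, 19.6%;
- six groups: 8.3%, 10.8%, 16.9%;
- all 70 carers in the model, controls given a constant fidelity value, four COS-P groups: 10.0%, 14.8%, 22.3%.

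Some of these group sizes fall outside 8 to 10; they hold the number of carers at 35 while the number of groups varies.

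**The case against.** The best defence is that little depends on this analysis. Fidelity is one of three exploratory moderators, no decision rule uses it, and the Discussion names burnout and perceived support as moderators but not fidelity. That stands, and it limits the importance of the point. It is also fair that a COS-P-arm-only regression is not literally what Statistical analyses describes. The planned model contains both arms, but coding controls to a constant gives similar error rates.

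An analysis plan might add a clustering correction. However, the article already fixes the predictor, the outcomes, the model type and the order of entry, and no correction creates more than about 2 df from four groups.

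Some stronger readings go beyond the documents:

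- *The error rate is certainly inflated.* It is inflated only if the ICC is positive. Shared sessions and facilitators make that plausible, but the protocol gives no value, and at 0.01 the rate is only about 6%.
- *There are exactly four values and about 30 surplus degrees of freedom.* The number of groups is derived. COS-P is offered to all foster carers as continuing education, so groups may include carers outside the study, and 35 study carers could then span more groups. The surplus is 31 with 35 carers but 24 with 28.
- *Fidelity is wholly confounded with the facilitator pair.* The text says two professionals co-facilitate, not that each group has its own pair.
- *Any stable group difference will be read as fidelity.* Only the part that happens to line up with the fidelity scores would be.
- *No valid test exists.* A test on group means holds its level; it has almost no power.

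**Conclusion.** The point holds as a unit-of-analysis error in the stated analysis. It is not a detail left to another document. A score shared by whole COS-P groups is tested against carer-level residual variation, on 33 df (26 with completers) where about four groups support 2.

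The size of the resulting error is conditional: about 5% at ICC 0, rising to about 24% at ICC 0.20 with 35 carers and four groups, and lower with more groups or fewer carers per group. These figures rest on an assumed ICC, a derived number of groups and one aggregate fidelity score per group. H1 and H2 are not affected by this point. It deserves correction because the change is cheap and the planned p-value is unreliable.

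**What to change.** 1. In Statistical analyses, remove fidelity from the carer-level hierarchical regressions and leave PBA and SAQ as the moderators there.
2. Report the fidelity score by COS-P group and session, beside each group's mean CCQ and PSI change. If a test is kept, take the COS-P group as its unit (about 2 df with four groups) and state that it has almost no power.
3. In the objective on moderators, reword so that fidelity is described and not tested as a moderator.

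This changes wording only; the 96 log items are already to be collected. The cost is one exploratory p-value that is not reliable with about four groups. Removing fidelity from these regressions also disposes of its being undefined for controls.

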### Qualitative measures

**Focus groups.** Two types of focus groups [45, 46] will be conducted:

*(a) With COS-P facilitators.* These focus groups will explore the subjective experiences of the social workers who facilitated the COS-P program. Drawing on their professional expertise and observations, facilitators will be asked to reflect on the appropriateness of the program for foster carers and the feasibility of implementing it within the French child protection system.

*(b) With foster carers.* Eight foster carers who participated in the COS-P intervention will be invited to participate in focus groups to discuss their experiences. These discussions will explore the perceived benefits and challenges of the program, and foster carers will be asked to share their perspectives on whether COS-P should be incorporated into pre-service or continuing education for foster carers. Participant recruitment will aim for diversity in terms of the age of children in their care, years of experience as a foster carer, and the number of children in the home. These focus groups will also provide valuable qualitative data relevant to the study’s complementary objectives, particularly regarding the foster carers’ experiences of emotional support and any potential iatrogenic effects of the intervention.

**Self-Confrontation Interviews.** Six foster carers will be invited to participate in self-confrontation interviews [47], in which they will view a video recording of themselves and their foster child participating in the MIM. This method will allow for in-depth exploration of the foster carers’ subjective experiences of the assessment and the impact of COS-P on their understanding of their foster child, their relationship with the child, and their approach to caregiving.

### Risks and iatrogenic effects

The COS-P intervention has been widely implemented in Europe, the United States, Australia, and other countries, and has been translated into eight languages. To date, no associated risks or negative effects have been reported [48]. A research monitoring committee composed of researchers and representatives from the Départment of Haute-Loire and accredited foster care agencies, will oversee the study to ensure ethical conduct and the well-being of all participants. Importantly, participation in the study will not affect foster carers’ or children’s access to usual psycho-educational support services.

### Statistical analyses

***Sample size and analysis.*** Sample size calculation was based on an effect size of *d* = 0.38, drawn from a meta-analysis examining the impact of attachment-based interventions on parental sensitivity [49]. An a priori power analysis using G*Power software [50] indicated that 58 participants are needed to achieve 80% power with a significance level of *p* <.05. To account for potential attrition (20%), we aim to recruit 35 participants for each group (intervention and waitlist control receiving TAU).

The data will be analyzed using both quantitative and qualitative methods. Statistical analyses will be conducted using R software. All tests will be two-tailed with a significance level set at *p* <.05.

***Quantitative analyses.*** Descriptive statistics will be used to characterize the sample at baseline (T1) and at each assessment point (T2, T3). This will include frequencies and percentages for categorical variables (e.g., gender) and means and standard deviations for continuous variables (e.g., age, duration of placement). To test the primary hypothesis (H1), a two-way mixed ANOVA will be conducted with Group (Intervention vs. Control) as the between-subjects factor and Time (T1, T2) as the within-subjects factor. The dependent variable will be the CCQ score. To test the secondary hypothesis (H2), a two-way mixed ANOVA will be conducted with Group (Intervention vs. Control) as the between-subjects factor and Time (T1, T2) as the within-subjects factor. The dependent variable will be the PSI score. To explore the potential moderating effects of parental burnout (PBA), perceived emotional support from placement services (SAQ) and fidelity of program implementation, hierarchical multiple linear regressions will be performed. The CCQ and PSI scores at T2 will be the dependent variables, with group allocation (Intervention vs. Control) as the primary predictor. The potential moderators (PBA, SAQ, and fidelity of implementation) will be entered in the model after the main effect of group allocation.

Complementary Analyses for a Subgroup of Foster Carers: A subgroup of 20 foster carers will participate in additional assessments using the Parent Development Interview - Revised (PDI-R) and the Marschak Interaction Method (MIM) coded with the Dyadic Emotional Interaction Style (D-EIS). These assessments will be conducted at T1 (baseline) and T2 (3-month follow-up).

Paired-samples t-tests will be used to compare the PDI-R and MIM-DEIS scores at T1 and T2 for the subgroup of foster carers. These analyses will explore the impact of the COS-P program on parental reflective functioning (as measured by the PDI-R) and on the quality of emotional dyadic interactions (as measured by the MIM-DEIS subscales) within this subgroup of foster carers.

***Qualitative analyses.*** Data from the self-confrontation interviews and focus groups will be analyzed using the Braun and Clarke thematic analysis approach [51]. This will involve a systematic process of identifying, coding, and categorizing patterns within the data. The aim is to develop a comprehensive understanding of participants’ experiences with the COS-P program and its perceived impact. Thematic analyses will be conducted using NVivo software.

***Data triangulation.*** Findings from the quantitative and qualitative analyses will be compared and contrasted to provide a richer and more nuanced understanding of the effects of COS-P in the context of foster care. This triangulation approach will enhance the validity and trustworthiness of the study findings.

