**Methods:**

This study protocol follows a mixed-methods randomized controlled trial evaluating the effectiveness of the COS-P program for foster carers in France. A total of 70 foster carers will be randomly assigned to either the intervention group (receiving COS-P in addition to Treatment as Usual) or the waitlist control group (receiving Treatment as Usual only). Quantitative measures, including the Caregiving Composite Questionnaire, Parenting Stress Index, and the Marschak Interaction Method, will be administered at baseline and at follow-up). Qualitative data will be collected through focus groups with foster carers and COS-P facilitators, and through self-confrontation interviews with a subset of foster carers.

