#### Primary hypothesis (H1)

Foster carers who participate in the COS-P program will demonstrate a significant improvement in caregiving sensitivity at the 3-month follow-up assessment, as measured by the Caregiving Composite Questionnaire (CCQ). Specifically, we hypothesize that, compared to the waitlist control group, foster carers completing COS-P will, at the 3-month follow-up assessment, show.

(H1a) a greater increase in parental mentalizing,

(H1b) a greater increase in parenting self-efficacy, and.

(H1c) more positive perceptions of the child.

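### The stated 80% power with 58 participants does not follow from d = 0.38 in a two-arm, two-tailed trial

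*Protocol article*

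**What the plan says.** The sample-size paragraph under Statistical analyses states: "Sample size calculation was based on an effect size of *d* = 0.38, drawn from a meta-analysis". The calculation is described as follows: "An a priori power analysis using G*Power software" "indicated that 58 participants are needed to achieve 80% power with a significance level of" p < .05. The recruitment target is 35 per group, to allow for 20% attrition, and the Abstract repeats the total: "A total of 70 foster carers will be randomly assigned".

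The same section fixes the test: "All tests will be two-tailed with a significance level set at *p* <.05", and "To test the primary hypothesis (H1), a two-way mixed ANOVA will be conducted with Group (Intervention vs. Control) as the between-subjects factor", with Time (T1, T2) as the within-subjects factor and the CCQ score as the dependent variable. The Primary hypothesis section frames the effect as change relative to the waitlist arm, for example "a greater increase in parental mentalizing". The treatment effect is therefore a between-arm difference in change.

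The article does not give the G*Power test family, the effect size as entered, or the pre-post correlation.

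**The concern.** For a two-arm, two-sided comparison, 58 is far too small a total for a standardised difference of 0.38. The effect size, power, significance level, sidedness, number of arms and total N are all stated, so this is a mismatch between stated figures and not a detail left to an analysis plan.

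The stakes lie in how the result will be read. The Discussion says that COS-P could enter pre-service or continuing education if it proves effective. A reader who trusts the 80% figure could take a non-significant result as evidence against an effect of 0.38 SD. At a correlation of 0.5 and with 56 analysed, the trial would miss a true effect of that size about seven times in ten.

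**Working it through.** **Inputs from the article.** d = 0.38; alpha 0.05, two-sided; power 80%; stated total 58 (29 per arm); 70 recruited; 20% attrition, so 70 x 0.8 = 56 analysed (28 per arm); primary test 2 groups x 2 times.

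**Assumptions.** Pre-post correlation rho not stated, range shown; equal SD at T1 and T2; equal arms; independent carers, with no allowance for delivery in groups.

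**1. Reproducing 58.** For the within-between interaction, the noncentrality is lambda = f² x N x m / (1 - rho), with df 1 and N - 2 and m = 2. Put in f = d/2 = 0.19 and rho = 0.5:
- N = 56: lambda = 0.0361 x 56 x 2 / 0.5 = 8.09, power 0.798
- N = 58: lambda = 0.0361 x 58 x 2 / 0.5 = 8.38, power 0.812

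So 58 is the first even total above 80%. Other routes, each at 80% power:

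| Route | Total N |
|---|---|
| Interaction, f = 0.19, rho = 0.5 | 58 |
| Two-group ANOVA, 0.38 entered as f | 58 |
| One-group paired t, 0.38 | 57 |
| Interaction, f = 0.38, rho = 0.5 | 16 |
| Between-groups factor, f = 0.19, rho = 0.5 | 166 |
| Two-sample t, d = 0.38, one-sided | 174 |
| Two-sample t, d = 0.38, two-sided | 220 |

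The two-group ANOVA has lambda = 0.38² x 58 = 8.38 and the same df as the interaction route, so the two cannot be told apart.

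**2. What those inputs imply.** In a 2x2 interaction, f = 0.19 means that each cell deviates by 0.19 SD, so the difference in change is 4 x 0.19 = 0.76 SD. As a check, a two-sample t on change scores at 0.76 SD with 29 per arm also has power 0.812 (at rho = 0.5 the SD of change equals the SD of the score). In a two-group ANOVA, d = 2f = 2 x 0.38 = 0.76. The paired route has no control arm.

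**3. What d = 0.38 requires.** A two-sample, two-sided t (noncentral t) has power 0.798 at 109 per arm and 0.801 at 110, so 220 in total. With 29 per arm its power is 29.6%.

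**4. Power of the planned test.** The SD of change is sqrt(2(1 - rho)) score SDs, so a 0.38 SD difference in change has standardised size 0.38 / sqrt(2(1 - rho)), tested with a two-sample t on change:

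| rho | Standardised size | N = 56 | N = 58 | N = 70 | Detectable difference, N = 56, 80% power |
|---|---|---|---|---|---|
| 0.3 | 0.321 | 22% | 22.5% | 26% | 0.90 SD |
| 0.5 | 0.380 | 29% | 30% | 35% | 0.76 SD |
| 0.7 | 0.491 | 44% | 45% | 53% | 0.59 SD |
| 0.8 | 0.601 | 60% | 61% | 70% | 0.48 SD |
| 0.85 | 0.694 | 72% | 74% | 82% | 0.42 SD |
| 0.87 | 0.745 | 78% | 80% | 87% | 0.39 SD |

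If d = 0.38 is instead meant in SDs of the change score, power at N = 58 is 29.6% whatever the correlation.

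**The case against.** The strongest defence is the correlation. The planned test uses each carer's own baseline, so a high pre-post correlation raises power well above that of a single comparison at T2: 61% at 0.8 with 58 analysed, and 82% at 0.85 if all 70 are analysed. The article gives no test-retest figure for the CCQ, so a high value cannot be ruled out. This stands as a reason to report a range. It does not rescue the sentence, because 58 delivers 80% only near 0.87, and the article claims no such value.

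A reader might also infer that 58 certainly arose from entering f = 0.19. The documents do not support that. The inputs are not stated, two routes give 58 identically, and a third gives 57. The error in the stated figure does not depend on which was used.

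Finally, the article does not say that a null result would be taken to show that COS-P fails, nor would a significant result necessarily overstate the effect. Inflation among significant results is a tendency that depends on the true effect.

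**Conclusion.** The point holds as a mismatch between stated figures: d = 0.38, two arms, two-sided 0.05 and 58 participants do not give 80% power. An ordinary comparison needs 220, nearly four times as many (220 / 58 = 3.8). For the planned Group x Time test with 58 analysed, power runs from 22.5% to 61% for correlations of 0.3 to 0.8. A flat figure of 30% is tempting, but for a difference in score SDs that test has 30% power only at a correlation of 0.5, so it should not be quoted without that condition. Entry of an effect size that corresponds to 0.76 SD is a likely explanation and no more.

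The results assume equal SDs at the two times, equal arms and independent carers. The sentence needs correcting because it is wrong as written and the correction is cheap.

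**What to change.** Replace the power sentence with the figure for the planned analysis and name the correlation, for example:

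> With 70 randomised and 20% attrition (56 analysed), the Group x Time test has about 29% power for a 0.38 SD between-arm difference in change if the pre-post correlation is 0.5 (22% at 0.3, 44% at 0.7, 60% at 0.8). The difference detectable with 80% power is about 0.76 SD at 0.5 (0.90 SD at 0.3, 0.59 SD at 0.7, 0.48 SD at 0.8).

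Drop the claim of 80% power for d = 0.38, so that a non-significant result is not read as excluding that effect. If the authors did rely on a correlation near 0.87, they should state it and its source. Figures for a baseline-adjusted ANCOVA belong here only if the primary analysis is changed to ANCOVA; the article plans a mixed ANOVA.

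The cost is a rewritten paragraph and a much less favourable stated power. No extra participants are asked for, and the pool of 170 carers named under Participants could not supply 220 in any case.

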#### Randomization

A simple randomization procedure will be conducted at T0 by an independent researcher not involved in the study, using computer-generated random allocation.

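### Recruiting 70 does not cover the stated 20% attrition: 56 carers would remain, two short of the plan's own 58

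*Protocol article*

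**What the plan says.** Three figures stand together in the protocol article under Statistical analyses (Sample size and analysis).

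- Required number: "58 participants are needed to achieve 80% power".
- Attrition and target: "To account for potential attrition (20%), we aim to recruit 35 participants for each group".
- Basis: "Sample size calculation was based on an effect size of *d* = 0.38", calculated in G*Power.

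The total of 70 is repeated in the abstract ("A total of 70 foster carers will be randomly assigned") and in the column heading of Table 4. No other attrition rate appears, and no rule is given for turning 58 into 70.

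The primary analysis is specified as follows: "a two-way mixed ANOVA will be conducted with Group (Intervention vs. Control) as the between-subjects factor and Time (T1, T2) as the within-subjects factor". Testing is two-sided at 5%. Allocation is by simple randomisation, so 35 per arm is the intended split and is not guaranteed.

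**The concern.** Attrition normally means the share of enrolled participants who are lost, so an allowance for it has to be divided out of the recruited number. Here the target seems to have been reached by adding 20% to the required number, which always gives too small a target. The sentence then claims a protection that 70 does not provide: at exactly the attrition the plan anticipates, the analysed sample falls below the plan's own requirement.

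What is at stake is the internal consistency of the sample size statement, and whether the stated 80% power still applies at the attrition the plan expects. The headline number of the trial rests on this sentence.

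**Working it through.** **Inputs from the article (Statistical analyses):** required N = 58; attrition 20%; 35 per group, total 70; d = 0.38; two-sided alpha 0.05; power 80%; 2 (Group) x 2 (Time) mixed ANOVA.

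**Assumptions, not in the article:** the power calculation was for the Group x Time interaction with f = d/2 = 0.19, and the T1–T2 correlation (rho) was 0.5. These affect only step 4 below.

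**1. Where the plan's 70 appears to come from**

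- Total: 58 x 1.20 = 69.6, rounded up to 70.
- Per arm: 29 x 1.20 = 34.8, rounded up to 35.

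Both match the stated target. The article does not show the step, so this is an inference.

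**2. What 70 delivers at 20% attrition**

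- 70 x (1 − 0.20) = 56, or 35 x 0.80 = 28 per arm.
- Shortfall against 58: 2.
- Attrition that 70 can absorb while keeping 58: (70 − 58)/70 = 12/70 = 17.1%.

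**3. What dividing out the attrition gives**

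- Total: 58/0.80 = 72.5, so 73.
- Per arm: 29/0.80 = 36.25, so 37, or 74 with equal arms.

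Steps 2 and 3 use only figures printed in the article.

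**4. Effect on power, under the assumptions above**

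The noncentrality parameter is lambda = f² x N x m/(1 − rho), with m = 2 time points. The reference distribution is F with 1 and N − 2 degrees of freedom.

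First, the plan's own figure. With rho = 0.5 and N = 58, lambda = 0.0361 x 58 x 2/0.5 = 8.375 and power is 81.2%. Searching over even totals, 58 is the first to reach 80%, which matches the article. Then the neighbouring values:

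| N analysed | lambda | Power (rho = 0.5) |
|---|---|---|
| 56 | 8.086 | 79.8% |
| 57 | 8.231 | 80.5% |
| 58 | 8.375 | 81.2% |

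Since the correlation is not stated, the same calculation over a range:

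| rho | Power at 56 | Power at 58 | Difference (points) |
|---|---|---|---|
| 0 | 50.6% | 52.0% | 1.4 |
| 0.3 | 65.6% | 67.1% | 1.6 |
| 0.5 | 79.8% | 81.2% | 1.4 |
| 0.7 | 95.0% | 95.6% | 0.6 |

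Differences are taken before rounding. Losing two carers costs between 0.6 and 1.6 points. The choice of correlation moves power by about 30 points between 0.3 and 0.7.

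**The case against.** The strongest objection is that nothing of consequence follows. With a correlation of 0.5, power at 56 is 79.75%, a quarter of a point under 80%, and one more analysable carer closes the gap. The 20% is itself a planning guess without a cited source, and the difference between tolerating 17.1% and 20% is well inside its uncertainty. All of this stands, and it limits the point to a correction of the text.

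The power figures also depend on a correlation and a test family that the article does not give. That stands too. The exact match at 58 makes 0.5 plausible, but it remains an inference, so the figures have to carry that label and a range.

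It could be said that 20% was meant as a share of the 58, so that about 12 losses were planned for. The text gives no such rule. If that was the intention, the expected loss among those recruited is 17%, and the sentence should say so.

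Nor is this something left to a fuller document: the article states a requirement, a loss rate and a target, and the three do not agree.

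A reader might go further and infer that the trial is materially underpowered, or that it must enrol 74. The documents do not support either inference from this error. The loss of power is about one point, and restating the tolerated attrition with 70 kept resolves the inconsistency equally well. The figure of 74 also presumes equal arms, which the stated method ("A simple randomization procedure will be conducted at T0") does not ensure; 73 is the strict minimum total.

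**Conclusion.** The point holds as an arithmetic inconsistency of small practical effect. The stated target of 70 leaves 56 after the stated 20% attrition, two below the stated 58, and nothing in the abstract, Table 4 or the sample size paragraph reconciles the figures. This part rests only on printed numbers.

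Two parts are conditional. That the target was obtained by multiplying by 1.2 is a likely reconstruction, not a documented step. The fall in power of about 1.4 points assumes the 2x2 interaction model with f = 0.19 and a correlation of 0.5. Whether 58 is itself well founded is a separate question, and this finding does not depend on the answer.

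**What to change.** Keep 70 and correct the sentence along these lines: *Recruiting 70 carers retains 58 for analysis with attrition of up to 17%; with 20% attrition, 56 would be analysed.* Then state the power for 56, together with the test family, effect size f and repeated-measures correlation that were entered in G*Power. If those were the interaction test, 0.19 and 0.5, the figure to report is about 79.8%. The cost is one or two sentences, with no change to design, recruitment or analysis.

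If recruitment is still open (the article gives 30 June 2025 as its completion date) and the sponsor prefers to keep the 20% allowance, the alternative is a target of 73, or 74 for equal arms. That is three or four more carers from the 170 in the source population, with the total updated in the abstract and Table 4.
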